### Costing Study

Two main types of costs (i.e. health services and consumer) will be combined to get the intervention costs for the three options being assessed in the trial. The ‘increased service utilization’ and ‘reduced neonatal and maternal mortality’ will be used as the main measure of effectiveness, and cost effectiveness is defined in terms of cost per additional birth by a skilled attendant and cost per neonatal and maternal death averted.

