**Methods:**

A pragmatic cluster randomized trial, with qualitative and economic studies, will be conducted in Jhang, Chiniot and Khanewal districts of Punjab, Pakistan, from February 2011 to May 2013. At least 29,295 pregnancies will be registered in the three arms, seven clusters per arm; 1) structured birth planning and travel facilitation, 2) structured birth planning, and 3) control arm. Trial will be conducted through the Lady Health Worker program. Main outcomes are difference in neonatal mortality and service utilization; maternal mortality being the secondary outcome. Cluster level analysis will be done according to intention-to-treat.

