## Background

### Burden of Neonatal and maternal mortality in Pakistan

Around four out of 30 million infants born each year worldwide die in the first 28 days of life and more than one quarter of deaths occur in the first 24 hours of birth [1,2]. Two out of three neonatal deaths occur in just 10 countries and Pakistan stands third among these countries [1]. In Pakistan the newborn mortality is 55 deaths per 1000 live births, infant mortality rate is 77 deaths per 1000 live births and maternal mortality ratio is 276 per 100,000 live births [3]. The new born babies and infants die mainly due to birth asphyxia, intra-uterine growth retardation, and acute infections [3-5]. The major causes of maternal deaths are hemorrhage, obstructed labor, puerperal sepsis and toxemia of pregnancy. Most of these causes are both preventable and treatable.

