The study size is adequate for valid measurement of differences in service utilization and neonatal mortality. However, to get valid measurement of differences in maternal mortality the required sample size is 66 (instead of 7) clusters per arm or 198 total in the trial (instead of 21). This more than ten-fold increase in sample size is not feasible to manage, so neonatal mortality is taken as the key pregnancy outcome indicator.

The proposed randomization does not allow asking and responding to individual preferences/convenience. So the trial will not answer the question what would happen if health services are able to offer intervention according to patient preferences/convenience. Further work will be needed to test the approaches sensitive to individual preferences, in the local programme setting.

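### The costing study builds maternal deaths into its main effectiveness measure, although the protocol says differences in maternal mortality cannot be validly measured at this trial size

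*Protocol article*

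**What the plan says.** The Costing Study section says that increased service utilization together with reduced neonatal and maternal mortality "will be used as the main measure of effectiveness". It then defines cost-effectiveness by "cost per additional birth by a skilled attendant and cost per neonatal and maternal death averted". It does not say whether neonatal and maternal deaths form one denominator or two, and it attaches no caveat to the maternal part.

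The section Addressing bias, error and limitations says that "to get valid measurement of differences in maternal mortality the required sample size is 66 (instead of 7) clusters per arm", calls such an increase unmanageable, and concludes "so neonatal mortality is taken as the key pregnancy outcome indicator". The abstract gives the same ranking, with "maternal mortality being the secondary outcome". The Background gives the national rates: "maternal mortality ratio is 276 per 100,000 live births" and "newborn mortality is 55 deaths per 1000 live births".

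**The concern.** The protocol demotes maternal mortality in the effectiveness analysis because the trial is too small to measure a difference in it. The costing study then restores that difference to main-measure status and, on one reading, divides by it. A ratio is a harder use of an imprecise difference than a plain comparison. When the denominator is close to zero the ratio becomes very large, and when it changes sign the ratio loses its ordinary meaning. A chance gap of a few deaths could make an intervention look very cheap per maternal death averted, or make it look harmful.

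Comparing the costs of the three strategies is one of the specific objectives, so this affects a stated aim of the project. It does not touch the neonatal mortality or service utilization comparisons.

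**Working it through.** **Inputs.**
- From Statistical considerations: 7 clusters per arm (21 over three arms); k = 0.17; 95% confidence (taken as two-sided 5%); 80% power; at least 1,395 women per cluster; 20% loss. After loss, 1,395 × 0.8 = 1,116 per cluster and 7 × 1,116 = 7,812 per arm. Without loss, 9,765 per arm.
- From the Background: p0 = 0.00276 maternal and 0.055 neonatal. Both are national rates per live birth, applied here to pregnancies as an approximation.
- Assumed: a 25% maternal reduction, so p1 = 0.00207. The protocol states 25% for neonatal mortality only, so 0% and 50% are shown as well.

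**Step 1: the protocol's own figure.** The unmatched cluster-trial formula is

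c = 1 + (1.96 + 0.84)² × [p0(1-p0)/m + p1(1-p1)/m + k²(p0² + p1²)] / (p0 - p1)².

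With m = 1,395, the bracket is 1.973e-6 + 1.481e-6 + 0.344e-6 = 3.798e-6, and the divisor is 0.00069² = 4.761e-7. So c = 1 + 7.849 × 7.977 = 63.6, or 64 clusters against the stated 66. This is close, so a 25% maternal reduction is probably near what the planners used. With m = 1,116 the formula gives 78.

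**Step 2: a separate maternal ratio, at minimum size.**
- Expected maternal deaths: 7,812 × 0.00276 = 21.6 in control and 7,812 × 0.00207 = 16.2 in an intervention arm, a difference of 5.4.
- Variance of the difference: Poisson part 21.6 + 16.2 = 37.7; between-cluster part 7 × 0.17² × (3.08² + 2.31²) = 3.0. Total 40.7, SD 6.4.
- Power: 5.4/6.4 = 0.845, and P(Z > 1.96 - 0.845) = 13%. It is 12% with a t reference, and 14-15% at 9,765 per arm.
- P(averted ≤ 0) with continuity correction: P(Z < (0.5 - 5.4)/6.4) = 22%.

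Simulation with gamma-Poisson counts and k = 0.17 agrees. Results for one comparison with control:

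| Women per arm | True reduction | P(averted ≤ 0) | Exactly zero | 95% range of averted |
|---|---|---|---|---|
| 7,812 | 0% | 53% | 6% | -13 to 13 |
| 7,812 | 25% | 22% | 4% | -7 to 18 |
| 7,812 | 50% | 4% | 1% | -1 to 23 |
| 9,765 | 25% | 19% | 4% | -7 to 21 |
| 9,765 | 50% | 2% | 1% | 1 to 27 |

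In the 7,812 and 25% row the median is 5. With a 25% reduction in both intervention arms, at least one of the two comparisons with control is zero or negative in 30-34% of trials. At 12-15% power, the 95% interval for deaths averted includes zero in roughly 85-88% of trials. In those trials an interval for cost per death averted has no finite bound.

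**Step 3: one ratio over combined deaths.** With a 25% reduction in both rates, expected neonatal deaths averted are 7,812 × (0.055 - 0.04125) = 107.4, against 5.4 maternal. The maternal share is 5.4/112.8 = 4.8%. The combined denominator is zero or negative in 0.4-0.6% of simulated trials. For neonatal deaths alone it is 0.5-0.7%.

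**The case against.** Five points can be made for the protocol.

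1. **The phrase is ambiguous.** Outcome indicators defines a single pregnancy outcome covering neonatal deaths, with maternal deaths in brackets, so one ratio over combined deaths is a natural reading. On that reading the denominator is stable. This point is sound and limits the concern. The wording still needs settling, and with a maternal share near 5% the combined ratio says almost nothing about mothers.

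2. **A reader might infer that the maternal ratio will often be undefined or negative.** That goes too far. Exactly zero deaths averted occurs in about 4% of trials at a 25% reduction. Zero or negative together occurs in about one in five, and in 2-4% at a 50% reduction. The unbounded interval is the usual problem; a failed point estimate is not.

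3. **The sample size is a floor.** Services are offered to all pregnant women in catchments of about 170,000. Reading Khanewal's crude birth rate of 21.5 as per 1,000 per year, and assuming it for every cluster, gives 170,000 × 0.0215 = 3,655 per cluster, or 25,585 per arm. The chance of a zero or negative denominator at a 25% reduction then falls to about 8%. How many women would be registered is unknown, so 19-22% applies to the stated minimum. The protocol's own 66-cluster statement is unaffected.

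4. **A reader might take the maternal ratio for the headline economic result.** The documents do not support that. The section ranks none of its ratios and names the skilled-birth ratio first.

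5. **A reader might fault the section for giving no method for uncertainty or negative increments.** A condensed article may leave that to a fuller plan, so it is no finding. Nor must the maternal ratio be abandoned: it can be shown with its uncertainty, provided it is not a main measure.

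None of these removes the conflict between the two sections.

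**Conclusion.** The concern holds in a limited form. The protocol gives main-measure status in the costing study to a difference that it says elsewhere cannot be validly measured with 7 clusters per arm, and it does not repeat that limitation there.

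The size of the problem depends on the reading. A separate maternal ratio would rest on about 5 deaths at the minimum trial size and would usually have no finite interval. A combined ratio would be stable but almost entirely neonatal. On neither reading does the trial yield a dependable cost per maternal death averted.

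The figures rest on the national maternal rate, k = 0.17 carried over to maternal deaths, and an assumed 25% reduction. The ratios per additional skilled-attended birth and per neonatal death averted can remain main measures, and the trial's main comparisons are unaffected.

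**What to change.** In the Costing Study section:
- Limit the main cost-effectiveness measures to cost per additional skilled-attended birth and cost per neonatal death averted.
- Report maternal deaths by arm as counts and rates with confidence intervals, labelled descriptive.
- Give any cost per maternal death averted only as exploratory, and state there that the trial has 7 of the 66 clusters per arm that the protocol says are needed.
- If a combined neonatal and maternal ratio was intended, say so explicitly.

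This costs wording only. One ratio loses main-measure status; data collection, sample size and trial conduct stay as they are.

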### Exploratory Qualitative Study

The study will collect data on a range of social, economic, service access and quality etc. factors from care providers as well as pregnant women and their families to assess the social and administrative feasibility of said interventions in the programme context and inform refinements before scaling-up to other parts of the country.

### Addressing bias, error and limitations

Comparing the socio-demographic and health services profiles of the three selected districts does not indicate any significant difference that can potentially lead to differences in care seeking behavior and/or quality of service. The proposed cluster randomization is expected to address the potential selection bias across the three trial arms.

The lack of masking (blinding) could introduce bias through two routes i.e. “incorrect measurement” and “leakage” from one group to another. There is a possibility of incorrect measurement of “service utilization” and “pregnancy outcomes” by the lady health worker, who is aware of the intervention allocation. This possibility of measurement bias will be reduced through better training and vigilant supervision of lady health workers as well as cross-verifying a sample of these measurements by the respective lady health supervisor (also research staff, where possible). Although this is possible, we believe this is unlikely that pregnant woman in the control arm would somehow get “structured birth planning” and/or “travel facilitation” from lady health worker in an intervention arm (i.e. LHW associated with another facility and serving some other population) leading to misinterpretation of results.

The possible poor quality of EmONC services available at the facilities could lead to an under-estimation of the potential gain from the trial interventions to address the decision and access delays. Before starting the trial, efforts will be made, mainly through programme but supplemented with minimal project inputs (if required), to make acceptable quality EmONC services available at the *twenty one* selected facilities. This facility support (if made available) will be same for all the facilities, thus not introducing any bias in the measurement of association. The cluster randomization will also ensure an acceptable distribution of any possible effect, of varied service quality, across three trial arms and thus avoiding getting any false association.

The study size is adequate for valid measurement of differences in service utilization and neonatal mortality. However, to get valid measurement of differences in maternal mortality the required sample size is 66 (instead of 7) clusters per arm or 198 total in the trial (instead of 21). This more than ten-fold increase in sample size is not feasible to manage, so neonatal mortality is taken as the key pregnancy outcome indicator.

The proposed randomization does not allow asking and responding to individual preferences/convenience. So the trial will not answer the question what would happen if health services are able to offer intervention according to patient preferences/convenience. Further work will be needed to test the approaches sensitive to individual preferences, in the local programme setting.

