### Study Setting

Two districts of Punjab i.e. Jhang and Khanewal have been selected for implementing the proposed trial. These are the districts where MNCH Programme or its partners have carried out the facility strengthening for EmONC services, have trained two or more batches of community midwives, and have a functioning network of lady health workers.

 · *Jhang* (recently divided into Jhang and Chiniot) is spread over an area of 8809 square kilometers, with an estimated population of about 3.5 million, and male to female ratio of 1.08. One quarter of the population is urban, whereas three quarters is rural. Total literacy rate is 37.12%, with 51.53% in males and 21.43% in females. The average household size is 6.5 with 85.9% dependency ratio. Currently married population is 62.2%.

 · *Khanewal* is spread over an area of 43494 square kilometers, with an estimated population of about 2,503,459 with 52% males and 48% females. The estimated population growth rate is 2.4%. The infant mortality rate is estimated to be 86/1000 which is higher than the provincial as well as the national figure of 77/1000. Total literacy rate is 45% and 33% of the population is living below poverty line. The crude birth rate is 21.5 and average household size is 6.9. It has four tehsils Khanewal, Mian Channu, Kabirwala and Jahanian.

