## **Discussion**

In Pakistan, the Ministry of Health is a policy development and national level planning body. It has established a Maternal and Newborn Health (MNH) Cell to coordinate integrate and streamline all MNH activities in the country. The district health offices are responsible for implementation, monitoring and management of healthcare delivery including MNCH, through a network of 40-60 bed Tehsil Head-Quarter hospitals (THQs), 20 bed Rural Health Centers (RHCs) and 4-6 Basic Health Units (BHUs) around each RHC. The provincial departments of health, in accordance with national policies and with support of the National MNCH Programme, have started: a) training community midwives for enhanced coverage of skilled birth attendants, and b) strengthening the RHCs and THQs for basic emergency obstetric care and district headquarter hospitals for comprehensive emergency obstetric care. These birthing and EmONC services are also being provided by private facilities in each district. However, the quality and cost of services at private facilities vary widely.

Currently at the community level, the birthing services are provided by a wide range of qualified, semi-qualified, and unqualified birth attendants. The coverage of qualified skilled birth attendant is still less than the semi- or non-skilled attendants. An increased utilization of the available skilled birth attendants implies that pregnant woman is: a) informed about the safe birthing options available, b) able to select the feasible choice, and then c) able to avail the feasible safe birthing services (when required). Similarly an increased utilization of EmONC care also implies that the woman is: a) informed about what emergency obstetric care may be required: when and from where, b) able to decide when and from where to seek EmONC care (if required), and then c) able to reach in-time the right facilities for EmONC care.

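### With seven clusters per arm, randomization alone does not ensure an acceptable spread of district and facility type; restrict the allocation on both factors, or adjust for them

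*Protocol article*

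**What the plan says.** The section on bias, error and limitations makes three linked statements.

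- On districts: "Comparing the socio-demographic and health services profiles of the three selected districts does not indicate any significant difference that can potentially lead to differences". The sentence goes on to limit this to differences in care-seeking behaviour or in the quality of service.
- On selection: "The proposed cluster randomization is expected to address the potential selection bias across the three trial arms".
- On service quality: "The cluster randomization will also ensure an acceptable distribution of any possible effect, of varied service quality, across three trial arms". The article adds that a false association is thereby avoided.

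Other sections give the facts against which these can be read.

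- The abstract sets the size: "At least 29,295 pregnancies will be registered in the three arms, seven clusters per arm".
- Study Setting profiles two areas. For Jhang, from which Chiniot was recently separated: "Total literacy rate is 37.12%, with 51.53% in males and 21.43% in females". For Khanewal: "Total literacy rate is 45% and 33% of the population is living below poverty line". Chiniot has no profile of its own.
- Study Population says that each cluster is built around either a THQ or an RHC. It does not say how many of each. The Discussion gives THQs 40 to 60 beds and RHCs 20.

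The article does not describe how clusters are allocated, and it mentions no stratification, matching or other restriction.

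**The concern.** These are positive claims about what the design delivers. Randomization balances the arms on average over all possible allocations. It does not guarantee balance in the one allocation that is drawn, and with seven units per arm the shortfall can be large.

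District and facility type are known before allocation. Both could plausibly bear on care seeking, access to emergency obstetric care and baseline mortality. Literacy is relevant to an intervention that works through information and planning. If one arm has most of the Khanewal clusters, or no THQ at all, the effect estimate for that trial is less precise than it could have been. Readers will also doubt the result, whichever way it falls. A text that promises an acceptable distribution removes the reason to use two factors that cost almost nothing to use.

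**Working it through.** **1. What the documents allow to be compared.** Two socio-demographic measures with a plausible bearing on care are given for both areas.

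| Measure | Jhang (with Chiniot) | Khanewal | Difference |
|---|---|---|---|
| Total literacy | 37.12% | 45% | 45 − 37.12 = 7.88 points |
| Mean household size | 6.5 | 6.9 | 0.4 |

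No significance test can be done from the text. The bias section refers to a comparison of three districts, but only two profiles are shown.

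**2. Inputs for the allocation check.**

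- From the article: 21 clusters, 3 arms, 7 per arm.
- Assumed: allocation without restriction.
- Assumed: 9 clusters in Khanewal and 12 in Jhang/Chiniot, from the populations in Study Setting. 21 × 2.5/(2.5 + 3.5) = 8.75, rounded to 9.
- Assumed: 5, 6 or 7 THQs among the 21, with a wider range checked below.

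**3. District.** The probability that the arms receive a, b and c Khanewal clusters (a + b + c = 9) is C(7,a) C(7,b) C(7,c) / C(21,9), with C(21,9) = 293,930.

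| Split | Number of allocations | Largest minus smallest arm |
|---|---|---|
| 3, 3, 3 | 35³ = 42,875 | 0 |
| 4, 3, 2 | 6 × 35 × 35 × 21 = 154,350 | 2 |
| 5, 2, 2 | 3 × 21³ = 27,783 | 3 |
| 4, 4, 1 | 3 × 35 × 35 × 7 = 25,725 | 3 |
| all others | 293,930 − 250,733 = 43,197 | 4 or more |

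- Difference of 3 or more: (27,783 + 25,725 + 43,197)/293,930 = 96,705/293,930 = 32.9%.
- Difference of 4 or more: 43,197/293,930 = 14.7%.

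**4. Facility type.** With T THQs, the probability that at least one arm has none is [3 C(14,T) − 3 C(7,T)] / C(21,T).

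- T = 5: (6,006 − 63)/20,349 = 29.2%.
- T = 6: (9,009 − 21)/54,264 = 16.6%.
- T = 7: (10,296 − 3)/116,280 = 8.9%.

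The message does not depend on the exact count. For T from 4 to 10, simulation puts a difference of three or more THQs between arms at 26% to 42%.

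**5. Both factors together.** With 9 Khanewal clusters and T from 4 to 8, the THQs spread over the districts in proportion, at least one factor is off by three or more clusters in 51% to 60% of simulated allocations. Both are within one cluster in only 2% to 7%.

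**6. Any other cluster-level characteristic.** The difference in means between two arms of seven has standard deviation √(1/7 + 1/7) = √(2/7) = 0.53 cluster SD. By the normal approximation it exceeds 0.5 SD in about 35% of allocations.

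**The case against.** The strongest reply is that a journal article condenses a fuller protocol, which may stratify. That stands: the allocation method is not described, so the percentages above hold only if allocation is unrestricted. A reader might infer that the trial uses simple randomization, and the article does not establish that. What remains is that the article rests its assurance on randomization itself and names no restriction that would support it.

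The wording is also more careful than a quick reading suggests. It denies only differences that matter for care seeking or service quality, and it promises an acceptable distribution, not exact balance. It would be wrong to say that the plan claims identical districts. One literacy gap does not disprove the qualified sentence, though it does undercut it.

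The facility contrast may be smaller than bed numbers imply. The Discussion puts RHCs and THQs together as sites strengthened for basic emergency obstetric care. Facilities are selected after a service assessment, and any support is to be the same for all 21. This reduces the difference but does not remove it, and the article itself allows for varied service quality.

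Three stronger readings are tempting and should not be adopted.

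- *Khanewal has higher mortality than Jhang.* The text says "The infant mortality rate is estimated to be 86/1000 which is higher than the provincial as well as the national figure of 77/1000", but gives no figure for Jhang or Chiniot, so it cannot show a difference between the trial districts.
- *Access distances differ greatly.* The printed areas imply 3.5 million/8,809 = 397 and 2,503,459/43,494 = 58 persons per square kilometre. The Khanewal area looks doubtful and should be checked; it is not evidence of a district difference.
- *The estimate will be biased.* Chance imbalance does not bias a randomized comparison over repeated allocations. A sound cluster-level interval reflects it, and the sample size already allows for between-cluster variation (k = 0.17).

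The effect on the estimate may also be modest. Purely for scale, suppose the two areas had rates of 86 and 77 per 1,000 (the second assumed). Arms with 4 and 2 Khanewal clusters would then have an expected ratio of (4×86 + 3×77)/(2×86 + 5×77) = 575/557 = 1.03. With 5 and 2 it is 584/557 = 1.05. Against a target reduction of 25% this is small but not negligible.

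**Conclusion.** The point holds as a moderate one about design and wording. With seven clusters per arm, randomization alone does not ensure an acceptable distribution of service quality, and the article's literacy figures and mixture of facility types weaken its statement on comparability. If allocation is unrestricted, a marked imbalance on district occurs in about one allocation in three (9 Khanewal clusters assumed). An arm without any THQ occurs in about 29% to 9% (5 to 7 THQs assumed). The consequence is lost precision and lost credibility for the realised allocation. The trial is not invalidated. If the full protocol already restricts allocation on these factors, what is left is to say so where the assurance is given.

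**What to change.** In the section on bias, error and limitations, replace the assurance with a statement of how the allocation is restricted. Use constrained randomization: accept only allocations in which the arms differ by about one cluster at most on each of district (Jhang/Chiniot against Khanewal) and facility type (THQ against RHC), and draw one at random. Under the assumptions above 2% to 7% of allocations qualify. There are C(21,7) × C(14,7) = 116,280 × 3,432, about 399 million, so even 2% leaves roughly 8 million to draw from.

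This is better than four separate strata of district by facility type. With few THQs, some strata could hold too few clusters to contain all three arms, and the strata would cost three degrees of freedom.

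Adjust the cluster-level comparison for the two factors. If allocation has already taken place, prespecify this adjustment only.

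The cost is wording, an allocation list and about two degrees of freedom: from 14 − 2 = 12 to 10 for a comparison of two arms, or from 21 − 3 = 18 to 16 for a model of all three. No extra participants, staff or data are needed, because both factors are known once the 21 facilities are chosen. The Khanewal area figure should be checked at the same time.
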